##### Aim #2

To compare the screening mammography self-reported barriers after 120-days post randomization between those receiving a mammography "implementation intentions" intervention (**MI**^**2**^) and those receiving only a general breast cancer prevention health education intervention (**C**).

The outcome for this aim, self-reported barriers, takes integer values from zero to eleven. To analyze this outcome, we will use a two-sample t-test. If gross non-normality is present and Wilcoxon Rank Sum test will be used. In addition to testing the main effect of treatment group, the interaction between treatment arm and 120-day breast cancer screening status will also be investigated to determine whether there is a greater reduction in barriers among screeners from the **MI**^**2 **^group relative to screeners from the **C **group. In the presence of serious imbalances despite the randomization, additional predictor variables can be incorporated into this analysis using multiple regression assuming the normality assumption holds. If not, appropriate power transformations will be used on the dependent variable prior to modeling.

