In general, health behavior theories assume a certain level of knowledge about the health issue in question. After all, people need to know something to form perceptions and attitudes about the behaviors that lead to or prevent disease. Lack of awareness of the issue defines the PAPM's first stage. In the second stage, people become aware but are not yet at a point where they are actively considering the precautionary behavior. An individual in this stage lacks engagement due to inadequate personal relevance. Perceived susceptibility is presumed to be important at this stage. If, and when, people become engaged in the issue, they progress to a decision-making phase (Stage 3). Self-efficacy, barriers, and any prior experience with the screening test might be important in this decisional stage. Decision-making can result in a decision not to act (Stage 4) or a decision to act (Stage 5). However, deciding to act is not the final step in the process. It is at the decisional point that new barriers or low self-efficacy can again become apparent and need to be addressed directly. We propose addressing these issues through an application of the "implementation intentions" construct and have labeled this Action Implementation Intentions in the gap between decision and test completion. Our prior work [50] and other studies [8] have shown that even once a decision has been made and individuals are motivated to complete cancer screening, many individuals still fail to follow through with volitional features of testing procedures. This gap between decision and action is not unique to the PAPM [25,51].

The development of plans to overcome specific logistic or perceptual barriers can facilitate the translation of intent into action. For breast cancer, the decision to get screened may be separate from the decision of where to go to obtain screening services. Multiple steps are clearly involved in following through with test scheduling, completion, and follow-up. Our proposed project will explore and define these constructs as they apply to breast cancer prevention; the culturally sensitive intervention will test the model and its assumptions, and a 120-day post randomization follow-up survey will confirm participant progression through PAPM stages, determine changes in reported breast cancer screening barriers, and evaluate response to implementation intentions among minority women.

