#### Project Instrumentation

The purpose of all survey project instrumentation is to collect data for use in developing individually tailored materials and to allow for analysis of study main effects with appropriate covariate controls. The measured constructs should also provide information on which variables are responsible for intervention effects. All measures except for "Implementation Intentions" measures will be given to study participants prior to randomization and thus to participants in both arms (**MI**^**2 **^and **C**).

Though many of the scales and instruments selected for the study have been used in previous studies, the complete baseline survey instrument will be pilot tested with Latina and female AI/AN community members within our two target communities. Feedback from this pilot testing phase will be used to revise the instrument and to prepare it for administration. Our goal is to establish an instrument that can be completed in 10-15 minutes using a notebook computer.

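### Aim 2 tests the 120-day barrier count without the baseline count taken from every woman, giving up precision that costs nothing

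*Protocol article*

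**What the plan says.** In the protocol article, the Aim #2 part of Data Analysis sets the target as a between-arm comparison at follow-up: "To compare the screening mammography self-reported barriers after 120-days post randomization between those receiving" the two interventions. It describes the variable: "The outcome for this aim, self-reported barriers, takes integer values from zero to eleven". It then names the test: "To analyze this outcome, we will use a two-sample t-test". The fallback is a Wilcoxon rank-sum test under gross non-normality, which also uses no baseline value.

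Covariates have one route in: "In the presence of serious imbalances despite the randomization, additional predictor variables can be incorporated into this analysis using multiple regression". Which predictors, and what counts as serious, are not stated. The opening paragraph of Data Analysis describes the balance check in terms of demographic measures.

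A baseline value exists for all participants. HLK-BH Part II has consenting women answer barrier questions. Project Instrumentation says that, apart from the implementation intentions items, "measures will be given to study participants prior to randomization and thus to participants in both arms". The 120-Day Post Randomization Follow-Up section has barriers asked again by telephone.

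Two places use the language of change. The Conceptual Model section says the follow-up survey will "determine changes in reported breast cancer screening barriers", and Aim #2 plans an interaction analysis to see "whether there is a greater reduction in barriers among screeners from the" intervention arm than among screeners in the control arm. Aim #2 specifies neither a baseline term nor a change score.

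**The concern.** A woman's earlier barrier count is usually among the best predictors of her later one. A test that ignores it leaves predictable between-woman variation in the error term, so the confidence interval for the arm difference is wider than it need be. Any chance difference between the arms in baseline barriers also passes, in part, into the estimate.

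Making adjustment depend on observed imbalance does not solve this. The gain from a prognostic baseline does not depend on imbalance being seen, and the trigger is undefined. The balance check is described for demographics, so it might never look at barriers. Choosing the model after seeing the data also leaves the Aim 2 analysis open.

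The sample was sized for screening completion (Aim 1) only. No power is stated for Aim 2, so there is no demonstrated reserve of precision to give away. The article states the test itself, so this is not a detail left to an analysis plan that is not shown.

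**Working it through.** **Inputs from the article** (Sample Size and Sample Size Justification): 121 analysed per arm, 80% power, two-sided α = 0.05, 15% against 30% screened; 290 randomised, 20% attrition. No standard deviation, effect size or correlation is given for barriers. I therefore work in SD units of the 120-day count and assume r, the baseline to 120-day correlation, at 0.3, 0.5 and 0.7.

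**Step 1: the plan's own figure.** For two proportions with pooled variance under the null and no continuity correction, the mean proportion is 0.225, and

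n = [1.960·√(2 × 0.225 × 0.775) + 0.842·√(0.15 × 0.85 + 0.30 × 0.70)]² / 0.15² ≈ 120.5, rounded up to 121 per arm.

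Power at 121 per arm is 80.2%. The stated figure reproduces, so 121 is a fair base for Aim 2.

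**Step 2: what the planned t-test can detect.** With 121 per arm and 80% power:

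d = (1.960 + 0.842) × √(2/121) = 0.360 SD.

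**Step 3: what adjustment changes.** In a linear model with the baseline count, the residual variance is (1 − r²) times the unadjusted variance. So:

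- detectable difference = 0.360 × √(1 − r²)
- equivalent gain in sample = 1/(1 − r²) − 1
- women per arm needed to match the t-test = 121 × (1 − r²), rounded up
- power at 0.360 SD = Φ(2.802/√(1 − r²) − 1.960)

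| Assumed r | Variance ratio | Equivalent gain in women | Effective n per arm | n per arm to match t-test | Detectable difference (SD) | Power at 0.360 SD |
|---|---|---|---|---|---|---|
| 0 (t-test) | 1.00 | none | 121 | 121 | 0.360 | 80.0% |
| 0.3 | 0.91 | 10% | 133 | 111 | 0.344 | 83.6% |
| 0.5 | 0.75 | 33% | 161 | 91 | 0.312 | 89.9% |
| 0.7 | 0.51 | 96% | 237 | 62 | 0.257 | 97.5% |

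**Step 4: the same with the stated attrition.** 290 × 0.8 = 232, or 116 per arm. The t-test then detects 0.368 SD. The adjusted model detects 0.351, 0.319 and 0.263 SD.

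**Step 5: is a change score as good?** No. Assuming equal SDs at the two times, its variance is 2(1 − r) times that of the t-test: 1.4, 1.0 and 0.6. At 0.360 SD and 121 per arm, its power is 65.8%, 80.0% and 95.1%. It is worse than the t-test below r = 0.5 and worse than the adjusted model at all three values.

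**The case against.** The strongest reply is that nothing here is invalid. Randomisation is at participant level, barriers are a secondary outcome, and an unadjusted t-test of the follow-up count is unbiased. Its standard error already allows for chance baseline differences, and no power target for Aim 2 is missed. This stands, and it limits the point to efficiency.

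Second, the test answers the stated hypothesis, which is fewer barriers in the intervention arm at follow-up. The wording about changes sits in the conceptual background, and the wording about reduction belongs to the interaction analysis. This is largely right. The case for adjustment does not need that wording, because the adjusted model estimates the same between-arm difference at 120 days. The interaction analysis, though, cannot speak of a reduction without a baseline term.

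Third, the conditional regression does not exclude baseline barriers, and Project Instrumentation foresees covariate control. True, but it neither names them nor guarantees them, and entry depends on an imbalance judged after the data are seen.

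Fourth, r is unknown and may be modest. Baseline is taken on a notebook computer and follow-up by telephone 120 days later, after education in both arms, and only portions of the questions are repeated. The instrument section names a 19-item susceptibility, benefits and barriers scale, while Aim #2 uses a count from zero to eleven. These are good reasons not to lean on the 96% figure. They do not turn the gain into a loss, and the model does not require the two scores to share a scale.

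Fifth, the stratum must be defined and non-normality handled. Both are fair demands on the wording of the fix.

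**Conclusion.** The concern holds. The article fixes an Aim 2 analysis that uses only the 120-day count, although barriers are measured before randomisation in both arms, and its conditional covariate rule does not bring that measure in reliably. The consequence is reduced precision on a secondary outcome, with no bias.

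The size rests on an assumed r. The gain is small at 0.3 (10% more women in effect, power from 80% to 83.6%) and material at 0.5 (33%, 89.9%). At 0.7 it is large (96%, 97.5%). The figures also assume a roughly linear relation between the two counts and a baseline value for every analysed woman. That some gain is available is well founded, but its amount is not known from the document. The change should be made because it costs almost nothing, and it does not call the Aim 2 comparison into question.

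**What to change.** Replace the Aim 2 main analysis with a linear model of the 120-day barrier count on arm, baseline barrier count and the randomisation stratum. Report the adjusted mean difference with its 95% confidence interval. State that baseline adjustment applies whatever balance is observed. Keep the t-test, or the rank-sum test under gross non-normality, as a supporting check.

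Three details belong in the same edit:

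- Say which stratum is meant. The Design section randomises within recruitment event, while the Aim 1 and Aim 3 models use community indicators. If some events are small, state in advance how they are pooled.
- Carry the baseline count into the arm-by-screening-status analysis, so that its wording about reduction has something to refer to.
- Confirm that the baseline and 120-day barrier scores come from the same items, and define how the zero-to-eleven count is formed.

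The cost is a few lines of analysis text. No extra data, visits or participants are needed.

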#### Hypothesis

Not up-to-date or never screened individuals who receive a mammography "implementation intentions" intervention (**MI**^**2**^) will be significantly more likely to complete a screening mammography test at 120 days post randomization than those receiving a general breast cancer prevention health education intervention (**C**).

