#### 120-Day Post Randomization Follow-Up

All **MI**^**2 **^and **C **participants will receive a follow-up telephone call from a CHW to reassess breast cancer screening status. For example, participants will be asked if screening was performed within the last 120 days since the initial intervention, and if so, when it was performed, and when the participant plans to have their next routine breast cancer screening examination. The CHW also will re-administer portions of the HLK-BH program questions via the telephone and ask questions regarding breast cancer testing utilization, breast cancer screening barriers, perceived breast cancer susceptibility, screening self-efficacy, and breast cancer risk status and reassess Precaution Adoption Process Model behavioral breast cancer screening stage. Program evaluation and satisfaction questions will also be asked of each participant near the end of this final assessment. By re-administering portions of the HLK-BH program questions at the 120-day post randomization follow-up, the research team will be able to evaluate the differential impact of the **MI**^**2 **^intervention compared to the **C **intervention on the primary (e.g., breast cancer screening utilization) and secondary outcomes (e.g., breast cancer screening barriers and progression through the PAPM stages). Refer to Figure 2 for an overview of the flow of research participants.

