#### Sample Size and Sample Size Justification

This study will utilize Latina and AI/AN female participants from two distinct communities with approximately 121 randomized participants per community to test the main effects of the **MI**^**2 **^vs. **C **arms at 120 days post randomization. For this study, a total of 290 subjects will be randomized to either the **MI**^**2 **^or **C **treatment arms (to account for a possible 20% attrition rate from randomization to 120 day follow up). It is anticipated that 30% of those in the **MI**^**2 **^group will receive their breast cancer screening within the 120 day study period compared to 15% in the **C **group. A total of 242 subjects (121 per study arm) would have 80% power to detect the anticipated difference in screening rate between the **MI**^**2 **^and **C **groups at the α = 0.05 (two-sided) type I error rate (Table 5). Assuming up to a 20% attrition rate based on the research team's prior studies in rural Kansas, a total of 290 subjects will be randomized to either the **MI**^**2 **^or **C **treatment arms (145 per treatment). Additional screening rates were examined for study power (Table 5) to select an adequate sample size to detect clinically relevant differences. Numbers contained in Table 5 demonstrate that the sample will have at least 80% power to detect clinically relevant differences. Similar tables to Table 5 were also compared with varying sample sizes, with the final sample size selected being the choice that optimized both study power with the logistical constraints.

**Table 5 T5:** Power estimates (%) for a sample size of 121 subjects per group with α = 0.05 (two-sided)

		Breast Cancer Screening - Implementation Intentions	
		25%	30%
Breast Cancer Screening	10%	87	97
		
Controls	15%	Not Relevant	80

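### The Aim 2 interaction compares barriers between screeners in the two arms, a subgroup defined by the primary outcome, so selection alone can create, hide or reverse a difference

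*Protocol article*

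**What the plan says.** The Aim #2 paragraph of the Data Analysis section describes the outcome as follows: "self-reported barriers, takes integer values from zero to eleven". The main analysis compares the randomised arms: "To analyze this outcome, we will use a two-sample t-test", with a rank test if the data are grossly non-normal.

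The paragraph then adds that "the interaction between treatment arm and 120-day breast cancer screening status will also be investigated". The stated purpose is "to determine whether there is a greater reduction in barriers among screeners from the" MI2 group relative to those from the C group.

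Three other places bear on this:

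- The section on the 120-day follow-up ranks the outcomes: "primary (e.g., breast cancer screening utilization) and secondary outcomes (e.g., breast cancer screening barriers and progression through the PAPM stages". Both are asked in the same telephone call.
- The Aim #1 hypothesis is that women given MI2 "will be significantly more likely to complete a screening mammography test at 120 days post randomization" than women given C.
- The sample size section puts figures on this: "It is anticipated that 30% of those in the" MI2 group will be screened within the period, against 15% in C.

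The article does not label the interaction as descriptive or limit how it may be interpreted.

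**The concern.** The interaction splits women by something that happens after randomisation and that the intervention is designed to change. Randomisation makes the two whole arms comparable. It does not make the screeners of one arm comparable with the screeners of the other.

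The split is also related to the quantity being compared. The background section on barriers to mammogram use presents barriers as a reason why women do not complete screening, and the description of the MI2 arm says the programme is meant to deal with barriers to follow-through. If MI2 brings in women whom barriers would otherwise have kept away, MI2 screeners and C screeners will differ in barriers even if MI2 alters nobody's barriers.

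What is at stake is the account of how the intervention works. A significant interaction, or a null one, would be read as evidence about mechanism among screeners when it may only reflect who became a screener in each arm.

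**Working it through.** **1. The plan's own figure.** Inputs from the sample size section: 121 per arm, 15% against 30%, two-sided 0.05. With mean proportion 0.225, power = Φ{[√121 × 0.15 − 1.96 × √(2 × 0.225 × 0.775)] / √(0.15 × 0.85 + 0.30 × 0.70)} = Φ{(1.650 − 1.157) / 0.581} = Φ(0.848) = 0.802. The stated 80% is reproduced, so the rates and numbers below are those that the plan relies on.

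**2. Size and make-up of the subgroup.** Screeners: 0.30 × 121 = 36.3 in MI2 and 0.15 × 121 = 18.2 in C. At most 15% of women would screen under both conditions, so at least (30 − 15)/30 = half of MI2 screeners would not have screened under C. It is exactly half if every C screener would also screen under MI2.

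**3. A hand example with no effect on barriers.** Assume that 15% screen under either arm (mean 2 barriers), 15% only under MI2 (mean 5) and 70% under neither (mean N). These means are assumptions; the documents give none.

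- MI2 screeners: (0.15 × 2 + 0.15 × 5)/0.30 = 3.5. C screeners: 2.0. Contrast among screeners: +1.5.
- MI2 non-screeners: N. C non-screeners: (0.15 × 5 + 0.70N)/0.85.
- Interaction = (3.5 − N) − [2.0 − (0.75 + 0.70N)/0.85] = 2.38 − 0.176N.
- This gives +1.50 at N = 5, +0.97 at N = 8 and +0.44 at N = 11.

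The screener contrast and the interaction are thus different quantities, and the second depends on the women who are never screened.

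**4. Simulation on 120-day scores.** Assumed: barriers with mean about 5 and SD 2.5, rounded and limited to 0–11; log-odds of screening falling linearly with barriers; the intercept in each arm set to give 15% and 30%; no effect of arm on any woman's barriers. There were 2,000,000 women per arm in each setting. The last column is a normal approximation for 36.3 and 18.15 screeners and 84.7 and 102.85 non-screeners. Differences are MI2 minus C, and the true value is 0 throughout.

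| Slope per barrier, C / MI2 | Screeners | Non-screeners | Interaction | Chance of p < 0.05 |
|---|---|---|---|---|
| 0 / 0 | 0.00 | 0.00 | 0.00 | 5% |
| 0.2 / 0.2 | +0.18 | +0.17 | +0.02 | 5% |
| 0.4 / 0.4 | +0.35 | +0.30 | +0.05 | 5% |
| 0.8 / 0.8 | +0.61 | +0.43 | +0.18 | 6% |
| 0.4 / 0.1 | +1.37 | −0.14 | +1.51 | 54% |
| 0.4 / 0 | +1.77 | −0.31 | +2.09 | 80% |
| 0.8 / 0.2 | +1.96 | −0.15 | +2.11 | 89% |
| 0.4 / 0.8 | −0.36 | +0.60 | −0.97 | 30% |

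**5. The same for change from baseline.** Assumed: baseline mean 5, SD 2; change mean −0.5, SD 1.5; screening depends on the 120-day level.

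| Slope, C / MI2 | Screeners | Interaction |
|---|---|---|
| 0.4 / 0.4 | +0.15 | +0.04 |
| 0.8 / 0.8 | +0.25 | +0.10 |
| 0.4 / 0 | +0.68 | +0.79 |
| 0.4 / 0.8 | −0.11 | −0.33 |

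If each woman's barriers stay as they were at baseline, the gap in change is zero. A positive value makes MI2 screeners look worse and a negative value makes them look better.

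**The case against.** The best defence has four parts.

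- **The analysis is ancillary.** It is something to be investigated on top of the main comparison. The Aim #2 hypothesis concerns all women by arm, and barriers are a secondary outcome. This stands, and it limits the severity. It does not remove the defect, because the stated purpose is to determine a difference among screeners.
- **The sentence speaks of a reduction.** Barriers are measured at baseline and again at 120 days, so change may be meant, although the t-test is described for the 0–11 score. This also stands. The text leaves open which is modelled, and on change the bias is smaller. It is not removed unless barriers are stable or unrelated to screening.
- **With equal slopes the interaction is almost unbiased.** Correct: at most 0.18 in these settings. The contrast among screeners, which the sentence sets out to interpret, is still off by up to 0.61. Equal slopes are also not an obvious assumption for a programme meant to help women past their barriers.
- **Caveats may sit in a fuller document.** Possibly, but the article fixes both the comparison and its inferential purpose.

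A reader might go further and infer a gap of about 1.5 barriers in favour of neither truth nor MI2. The documents do not support any such figure. It rests on assumed means, it is a contrast of 120-day levels among screeners rather than the interaction, and as a reduction it would be zero if barriers were stable. Nor do they support saying that the bias flatters MI2: in most of these scenarios it hides a benefit. A reader might also infer that the mammogram itself distorts the comparison. The documents do not show this, and a shift equal in both arms would cancel.

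**Conclusion.** The point holds as a defect of one additional analysis under a secondary aim. Screeners in the two arms are not comparable by randomisation, and the arm by screening status term has no randomised interpretation. That follows from the plan's own outcome ranking, hypothesis and rates and needs no assumed figure.

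The size and sign do need assumptions. With no effect of MI2 on barriers, the scenarios give an interaction bias on 120-day scores from near zero (equal slopes) to about −1.0 or +2.1 (unequal slopes), and about −0.3 to +0.8 for change from baseline. With no link between barriers and screening it is zero.

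The primary analysis, the randomised Aim 2 comparison and the sample size are untouched. A reader should not infer that Aim 2 as a whole is biased.

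**What to change.** State that conclusions on Aim 2 rest on the comparison of all women by randomised arm. Then either delete the interaction or replace it with wording such as: *Barrier scores at baseline and 120 days will be tabulated by arm and 120-day screening status for description only. No p-value will be given and no statement will be made about the effect of MI2 among screeners.*

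Optionally, add arm by a baseline moderator already collected before randomisation (baseline barriers or prior screening), labelled exploratory. This answers a different question and does not replace the deleted one.

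The cost is the loss of one ancillary inferential test and a change of wording. Data collection, sample size and the primary analysis do not change.
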